## Abstract

**Background:**

Uncertainty exists regarding the optimal method to estimate glomerular filtration rate (GFR) for disease detection and monitoring. Widely used GFR estimates have not been validated in British ethnic minority populations.

**Methods/design:**

Iohexol measured GFR will be the reference against which each estimating equation will be compared. The estimating equations will be based upon serum creatinine and/or cystatin C. The eGFR-C study has 5 components:

1) A prospective longitudinal cohort study of 1300 adults with stage 3 chronic kidney disease followed for 3 years with reference (measured) GFR and test (estimated GFR [eGFR] and urinary albumin-to-creatinine ratio) measurements at baseline and 3 years. Test measurements will also be undertaken every 6 months. The study population will include a representative sample of South-Asians and African-Caribbeans. People with diabetes and proteinuria (ACR ≥30 mg/mmol) will comprise 20-30% of the study cohort.

2) A sub-study of patterns of disease progression of 375 people (125 each of Caucasian, Asian and African-Caribbean origin; in each case containing subjects at high and low risk of renal progression). Additional reference GFR measurements will be undertaken after 1 and 2 years to enable a model of disease progression and error to be built.

3) A biological variability study to establish reference change values for reference and test measures.

4) A modelling study of the performance of monitoring strategies on detecting progression, utilising estimates of accuracy, patterns of disease progression and estimates of measurement error from studies 1), 2) and 3).

5) A comprehensive cost database for each diagnostic approach will be developed to enable cost-effectiveness modelling of the optimal strategy.

The performance of the estimating equations will be evaluated by assessing bias, precision and accuracy. Data will be modelled as a linear function of time utilising all available (maximum 7) time points compared with the difference between baseline and final reference values. The percentage of participants demonstrating large error with the respective estimating equations will be compared. Predictive value of GFR estimates and albumin-to-creatinine ratio will be compared amongst subjects that do or do not show progressive kidney function decline.

**Discussion:**

The eGFR-C study will provide evidence to inform the optimal GFR estimate to be used in clinical practice.

**Trial registration:**

ISRCTN42955626.

## Background

Chronic kidney disease (CKD) is prevalent in the general population [1-4] and is commonly identified using estimation of glomerular filtration rate (GFR) or detection of protein in urine (albuminuria/proteinuria). GFR is accepted as the best overall measure of kidney function and is central to diagnosis, staging and management of CKD. Ideally GFR would be measured using reference procedures which follow the clearance of an infused exogenous substance (e.g. inulin, ^125^I-iothalamate or iohexol [5]). However, these methods are cumbersome and impractical for general kidney disease detection and management. Estimation of GFR (estimated GFR [eGFR]) using equations based on serum creatinine with adjustments for age, gender and race are widely used as surrogate measures of GFR. In England, the National Institute for Health and Care Excellence (NICE) have recommended which people should be tested for the presence of CKD (e.g. those with diabetes or hypertension) and that GFR should be estimated 6-monthly in people with stage 3 CKD (GFR 30–59 mL/min/1.73 m^2^) [6], comprising approximately 6-7% of the overall UK population [3,7]. The aim of disease detection is to identify and manage those most likely to progress to kidney failure and/or those at high risk of morbidity and mortality. In addition to the accurate identification of CKD, the ability of tests to identify which individuals with CKD will have high risk (i.e. progressive or mortal) disease is a crucial issue. Many people with stage 3 CKD are not at increased risk of progressive disease and there are concerns that CKD detection using creatinine-based approaches may be identifying individuals who are at low risk and unlikely to benefit from active management and inappropriate surveillance [8]. Recently, newer equations utilising cystatin C instead of, or in addition to, creatinine have been proposed. Given the high costs of cystatin C testing compared with creatinine, it is critical that its diagnostic accuracy and prognostic ability are carefully validated ahead of widespread introduction into the National Health Service.

### Measuring GFR

Standard clearance of inulin, including urine collection, remains the ‘gold-standard’ method for GFR measurement but few studies use this. Most evaluations of GFR equations have used radiolabelled plasma clearance methods which are assumed to be closely related to inulin clearance. Radiolabelled iothalamate plasma clearance was the method used for developing the Modification of Diet in Renal Disease (MDRD) Study [9] and Chronic Kidney Disease Epidemiology Collaboration (CKD-EPI) [10] GFR-estimating equations (see below), whilst the CKD-EPI equation validation dataset also used a variety of other reference GFR methods including iohexol [10]. Although regarded as the reference approach to assessment of kidney function, it is increasingly appreciated that non-inulin plasma clearance methods are not all equivalent [11]. Furthermore, as with any physiological measurement, GFR has an intrinsic biological variability, the understanding of which is critical to appreciation of disease-related change. Using a variety of reference markers, values (coefficient of variation, CV%) ranging between 5.5% and 11.6% have been reported for the biological variation of GFR [12-18]. However, most of these estimates were not derived using classical biological variation studies [19].

### Estimating GFR

Use of the MDRD Study equation (MDRD) [9,20,21], which estimates GFR adjusted for body surface area (BSA), has been endorsed by national professional healthcare organisations [6,22]. However, accuracy of the equation is sub-optimal. In the CKD field, accuracy of GFR estimating equations is commonly expressed as the P_30_, the percentage of eGFR values within 30% of ‘true’ GFR. This metric captures aspects of both imprecision (measurement error) and bias (systematic over- and/or under-estimation). Reported P_30_ values for the MDRD equation typically range between 73% to 93% [23]. The MDRD equation has also been criticised on the basis that it significantly underestimates GFR (particularly in individuals with GFR greater than 60 mL/min/1.73 m^2^) and has poor precision [10].

A revised equation, the Chronic Kidney Disease Epidemiology Collaboration (CKD-EPI_creatinine_) produces less biased estimates of GFR at higher levels of kidney function [10], although reportedly less accurate estimates as GFR falls below 60 mL/min/1.73 m^2^[23]. P_30_ values for the CKD-EPI_creatinine_ equation are slightly superior to those of the MDRD equation in studies that have undertaken a head-to-head comparison [23]. Cystatin C has been proposed as an improved marker of GFR compared with creatinine [24,25]. Recently, the CKD-EPI Collaboration have published two further CKD-EPI equations; one based on cystatin C (CKD-EPI_cystatin C_) and one using both cystatin C and creatinine (CKD-EPI_cystatin and creatinine C_) [26]. In the external validation datasets of Inker et al. [26] the CKD-EPI_cystatin C_ and CKD-EPI_cystatin and creatinine C_ equations achieved P_30_ values of 86% and 92% respectively. There has been little independent validation to date of these latter equations [27,28]. Amongst older people the MDRD equation achieved a P_30_ of 81% compared with 86% for the CKD-EPI_cystatin and creatinine C_ equation [27].

### Estimating GFR in British ethnic minority populations

People from South Asian and African-Caribbean backgrounds are at 3 to 5-fold increased risk of developing established renal failure compared with Caucasians. Whilst GFR-estimating equations have been validated in African-Caribbean communities from North America [29] and endemic Asian populations [30-35] there is no independent validation in British African-Caribbean populations; and no data at all amongst people originating from India, Pakistan, Sri Lanka and Bangladesh). There is some evidence that the black ethnicity coefficients in GFR estimating equations developed for use amongst African-Americans may not be transferable to other populations of African ancestry [36,37].

### Progression of kidney disease

There is no consistent definition of what constitutes renal progression in the literature. Many studies have used a doubling of serum creatinine, corresponding to an approximate halving of GFR, as an end-point defining progression, but this is insufficiently sensitive to be useful in clinical practice. Kidney Disease Improving Global Outcomes (KDIGO) have defined progression as a move to a higher disease category (e.g. stage 3A [GFR 45–59 mL/min/1.73 m^2^] to stage 3B [GFR30-44 mL/min/1.73 m^2^]) confirmed by a fall in GFR of greater than or equal to 25%, an increase in albuminuria, a greater than 25% decline in GFR (e.g. a decline from 60 mL/min/1.73 m^2^ to less than 45 mL/min/1.73 m^2^) or a greater than 10%/year decline in GFR (e.g. a decline from 60 mL/min/1.73 m^2^ to less than 54 mL/min/1.73 m^2^ in one year) [38]. NICE defined progression as a decline in GFR of more than 5 mL/min/1.73 m^2^/year, or more than 10 mL/min/1.73 m^2^ averaged over 5 years [6].

Progression is not necessarily common even amongst people with known CKD e.g. amongst people with stage 3 CKD only 1.3% progressed to stage 5 CKD (established renal failure, typically requiring dialysis or transplantation) over 5 years [39]. Amongst community dwelling older (greater than 65 years) adults with stage 3 CKD mean GFR declines of 3.6 mL/min/1.73 m^2^/year and 2.8 mL/min/1.73 m^2^/year have been reported respectively in male and female subjects with diabetes and somewhat lower values amongst subjects without diabetes (1.9 mL/min/1.73 m^2^/year and 1.1 mL/min/1.73 m^2^/year amongst males and females respectively) [40]. In the REIN study proteinuric (greater than 1 g/24 h) non-diabetic subjects with GFRs in the approximate range 30–50 mL/min/1.73 m^2^ showed a decline of GFR of 7.0 mL/min/1.73 m^2^/year with slightly lower values being observed in those receiving renin-angiotensin-aldosterone system (RAAS) blockade [41].

There are some data, mainly restricted to small studies in people with diabetes, describing disease progression in terms of decline in reference GFR measurements [42,43]. Generally, disease progression in people with diabetes has been described as following a broadly linear decline, being influenced by blood pressure and albuminuria and ameliorated by antihypertensive medication/RAAS blockade [42,44,45]. A similar pattern has been observed using estimated rather than measured GFR [46].

### Identifying progressive kidney disease

A significant problem is the ability of GFR-estimating equations to identify progression of kidney disease against background change in GFR (i.e. that due to ‘normal’ ageing; commonly cited as approximately minus 1 mL/min/1.73 m^2^/year) given the biological and measurement variability of both reference and estimated GFR. The intraindividual variation (CV_I_) of the main determinant (serum creatinine) of eGFR has been reported as 4.3% [47] to which should be added intralaboratory imprecision (CV_A_) of approximately 3.0% [22]. On this basis, the critical difference or reference change value (RCV) for serum creatinine is 13% (i.e. this is the difference that can be considered ‘real’ with 95% probability). The power function in the MDRD equation (-1.154, Table 1) increases the impact of CV_I_ to an average of 5.4%. Consequently the RCV for eGFR derived using the MDRD equation becomes 14.4%. As an example of this, in an individual a GFR of 60 mL/min/1.73 m^2^ will need to fall below 51 mL/min/1.73 m^2^ before it can be confidently considered a significant decrease. Some [48,49], although not the majority [50-53] of data suggests that the biological variation of serum cystatin C is greater than that of creatinine. If this were the case then it would clearly impact on the ability of cystatin C based GFR-estimating equations to detect changes in true GFR vis-à-vis serum creatinine.

**Table 1 T1:** Equations to be used to estimate glomerular filtration rate (GFR)

**Abbreviation**	**GFR equation expressed as a single equation**
MDRD [20]	175 × Scr ^-1.154^ × age^-0.203^ × 0.742 [if female] × 1.212 [if black]
CKD-EPI_creatinine_[10]	141 x min(Scr/κ, 1)^α^ × max(Scr/κ, 1)^-1.209^ × 0.993^Age^ × 1.018 [if female] × 1.159 [if black], where κ is 0.7 for females and 0.9 for males, α is -0.329 for females and -0.411 for males, min indicates the minimum of Scr/κ or 1, and max indicates the maximum of Scr/κ or 1
CKD-EPI_cystatin C_[26]	133 × min(Scys/0.8, 1)^-0.499^ × max(Scys/0.8, 1)^-1.328^ × 0.996^Age^ × 0.932 [if female] where min indicates the minimum of Scr/κ or 1, and max indicates the maximum of Scr/κ or 1.
CKD-EPI_cystatin-creatinine_[26]	135 × min(Scr/κ, 1)^α^ × max(Scr/κ, 1)^-0.601^ × min(Scys/0.8, 1)^-0.375^ × max(Scys/0.8, 1)^-0.711^ × 0.995^Age^ × 0.969 [if female] × 1.08 [if black] where κ is 0.7 for females and 0.9 for males, α is -0.248 for females and -0.207 for males, min indicates the minimum of Scr/κ or 1, and max indicates the maximum of Scr/κ or 1.

*Abbreviations:* CKD-EPI Chronic Kidney Disease Epidemiology Collaboration, MDRD Modification of Diet in Renal Disease, Scr serum creatinine, Scys serum cystatin C.

GFR changes of this order exceed the limit that most nephrologists would consider a clinically insignificant change. However, there are no prospective longitudinal data assessing the relative abilities of GFR-estimating equations to detect change in underlying measured GFR. One recent study has addressed the accuracy of GFR estimating equations compared with ^125^I-iothalamate measured GFR over time in people with kidney disease [54]. The authors concluded that GFR estimating equations accurately reflected changes in measured GFR over time. The study was robust (3,532 participants with CKD followed for a mean of 2.6 years) but retrospective in nature, and did not include data derived using cystatin C [54]. Observational data suggests that for identification of progressive CKD the combination of eGFR using cystatin C and albumin-to-creatinine ratio (ACR) ranks highest, followed by eGFR using cystatin C alone, then the combination of ACR and eGFR using creatinine, and finally eGFR using creatinine alone [55].

### Objectives of the eGFR-C study

Whilst there is a significant literature describing the accuracy of creatinine-based eGFR against reference methods, there are no studies addressing the ability of GFR estimating equations, including those incorporating cystatin C, to detect change in GFR. Furthermore, there are no data addressing the accuracy of these equations in black and minority ethnic populations. The eGFR-C study will evaluate the performance of GFR-estimating equations, including novel equations incorporating cystatin C, in assessing and monitoring measured GFR in people with stage 3 CKD. The data will be analysed to assess the impact of ethnicity, proteinuria and diabetes on equation performance. eGFR-C will assess whether eGFR using either creatinine or cystatin C or a combination of both is superior at detecting changes in GFR as measured by a reference GFR method. The utility of baseline eGFR and urinary ACR to predict which people are likely to show progressive kidney disease will also be tested. A simple economic evaluation of the relative costs of the diagnostic tests will be included to enable cost-effectiveness modelling.

## Methods/design

eGFR-C is a study which will provide the required evidence to identify the optimal estimate of GFR to use in clinical practice (Figure 1).

**Figure 1 F1:**
[figure not shown]
General study schema.

There are five components to the study:

1) A 3-year prospective longitudinal cohort study using 6-monthly estimates of GFR and baseline and final reference GFR values to assess and compare the accuracy and precision of each estimate of GFR and change in GFR. This will include assessments in high risk subgroups and ethnic groups.

2) Investigation and modelling of patterns of progression of GFR in a subset of the cohort, stratified by ethnicity, presence of diabetes and proteinuria, who will receive annual reference GFR, assessing risk factors and over time.

3) A sub-study investigating sources of variability to estimate the components of measurement error in each measure and estimate of GFR.

4) Using information from 1), 2) and 3) modelling of alternative monitoring strategies, using different estimates of eGFR and monitoring frequencies.

5) A model-based cost-effectiveness analysis.

### Prospective longitudinal cohort study

The primary study will comprise a prospective longitudinal cohort study in which adults (n = 1300) with stage 3 CKD, enriched to include people more likely to have progressive kidney disease (i.e. those with proteinuria and/or diabetes), will be recruited from six UK centres. Participants will be recruited from both primary (two centres) and secondary/tertiary (four centres) care. People aged 18 years and older having stage 3 CKD (eGFR measurements between 30 and 59 mL/min/1.73 m^2^ inclusive sustained over at least 3 months prior to recruitment) will be included. Recruitment will be targeted such that 20% to 30% of recruits will have proteinuria (ACR ≥30 mg/mmol) and a similar proportion will have diabetes. The prevalence of proteinuria and diabetes will be monitored during the course of the study to ensure reasonable representation.

Participants will attend hospital in the morning having been advised to consume a light breakfast (no meat or fish). A clinical (including cardiovascular) and drug history will be recorded using a standardised questionnaire. Information on ethnicity will be gathered using a modified version of the 2011 UK Census Questionnaire. Height will be measured to the nearest 0.1 cm with a rigid stadiometer. Body weight will be measured in light indoor clothing to the nearest 0.1 kg. Waist circumference will be recorded to the nearest 0.1 cm at the mid-point between the lower costal margin and the level of the anterior superior iliac crest. Hip circumference will be measured at the widest point of the hips and the maximal protrusion of the gluteal muscles. Brachial blood pressure will be measured three times in the sitting position as recommended [56]. Blood will be taken for serum creatinine, cystatin C and a urine sample will be collected for ACR. Further aliquots of serum, plasma and urine will be stored for potential analysis of future markers of GFR. An iohexol reference GFR measurement will be undertaken in addition to estimation of GFR using four GFR estimating equations (MDRD, CKD-EPI_creatinine_, CKD-EPI_cystatin_, and CKD-EPI_cystatin-creatinine_) (Table 1).

Participants will be followed for three years. All the above measurements and the clinical questionnaire will be repeated at 36 months. At each 6 month interval, all participants will have blood taken for serum creatinine, cystatin C and a urine sample will be collected for ACR. GFR will be estimated as above.

Participants will be excluded if they are pregnant, have a history of untoward reactions to iodinated contrast media, have life expectancy which makes study completion unlikely [57], are unable to consent due to cognitive impairment, are whole- or part-limb amputees, have a recent (last 6 months) episode of acute kidney injury (as defined by the Acute kidney Injury Network criteria [58]) or have sickle cell disease.

GFR will be measured using an iohexol clearance method. A 5 mL bolus of Omnipaque 240 (518 g/L iohexol corresponding to 240 g/L of iodine, GE Healthcare http://www.gelifesciences.com) followed by 10 mL of normal saline will be injected into the antecubital vein. Blood samples will be collected at 5, 120, 180 and 240 minutes after injection. Samples will be stored at -80°C prior to analysis. Iohexol will be determined using isotope dilution mass spectrometry (ID-MS) [59] and GFR calculated [60]. Serum and urinary creatinine will be measured using ID-MS and enzymatic assays respectively, both traceable to a reference methodology. Serum cystatin C will be measured using a nephelometric immunoassay with calibration traceable to the international certified reference material ERM-DA471/IFCC [61]. Urinary albumin will be measured using a nephelometric immunoassay.

Blood samples will be collected using standard venepuncture and phlebotomy procedures and samples will be transported to the local laboratory, where plasma/serum will be separated within 4 h of venepuncture. Aliquots of serum/plasma and urine will then be stored at -80°C pending transportation to the central laboratories and analysis. Clinicians and others involved in patient care will be blinded to the specific study measurements (reference [iohexol] GFR, estimated GFR and ACR) for the duration of the study.

### Sub-study of patterns of disease progression

At three centres 125 each of Caucasian, African-Caribbean and Asian subjects (i.e. n = 375 in total), stratified in each group by higher and lower risk of disease progression (approximately 60 with diabetes and/or proteinuria and 60 with neither diabetes nor proteinuria) will undergo additional sampling every year over the 3 year study period. At each point indicated subjects will undergo a reference GFR measurement in addition to cystatin C and creatinine eGFRs and ACR. The study will enable a model of disease progression to be developed based on reference GFR measurement enabling optimal monitoring frequencies in a high-risk cohort to be defined. This number of subjects should provide a range of values over the main factors considered to influence disease progression and allow assessment of covariates in the statistical model. Further assessment of covariates will be performed by combining the data from this sub-study with the main study. Inclusions/exclusions and laboratory methods for this sub-study will be as above.

### Study of intra-individual biological variability

A study will be undertaken to define the normal biological variability of a reference GFR test in addition to the eGFR tests. Twenty people with stage 3 CKD will undergo four iohexol reference measures of GFR in four successive weeks, with standardisation for time of day (morning after a light breakfast) and day of week. Inclusions/exclusions and laboratory methods for this sub-study will be as above.

### Sample size calculations

1) Prospective longitudinal cohort study

The sample size calculation for the main study focuses on the ability to detect differences in accuracy of measurement between the MDRD_creatinine_ equation and the CKD-EPI_cystatin C_ equation. We will also make secondary comparisons with the other equations**.** The measure of accuracy we will use is the P_30_. Sample size is based on a simulation study to estimate differences in P_30_ and estimates of rate of change which are not amenable to algebraic solution. Our simulation modelled the full structure of the study including random variability, and computed statistical power through noting the percentage of simulations yielding statistically significant results (P < 0.05) for analysis of each outcome. Power estimates are based on 1000 simulations.

With 1000 evaluable subjects our simulations showed the study to have 87% power at the 5% significance level to detect a difference of 5% in P_30_, between 81% and 86%, which is of a magnitude considered clinically important and likely to occur with the expected scale of differences in imprecision between the equations [27]. We thus aim to recruit 1300 people, which allowing for 15-20% drop-out will deliver over 90% power. The proposed sample size in the ethnicity subgroups will allow P_30_ estimates to be reported with 95% confidence intervals of 10 percentage points wide.

Rates of change in estimated and measured GFR will be obtained by linear regression. Padala et al. proposed two cut-points for estimating accuracy of rates of change: greater than 3 mL/min/1.73 m^2^/year error and greater than 5% error [54]. The study will have over 90% power and over 80% power at the 5% significance level to detect differences in these two outcomes respectively, for differences of a magnitude corresponding with P_30_ measures of 81% and 86%.

2) Sub-study of patterns of disease progression

A sample size of 375 was chosen based on practical considerations to allow investigation of twelve covariates of interest (gender, age, diabetes, duration of diabetes, ethnicity, albuminuria, baseline GFR, blood pressure, body mass index, waist circumference, smoking status and presence of vascular disease) in addition to variables for time, drug effects and random effects. Another consideration was to include a reasonable number of subjects in each of the ethnic groups and high and low risk subgroups to estimate disease progression.

3) Study of intra-individual biological variation

The biological variation of GFR has been estimated at approximately 10% (see above). On this assumption, the sample size (n = 20) and number of repeat samplings proposed will enable the CV_I_ to be estimated within ±2% of its true value.

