#### Sub-study of patterns of disease progression

##### **How does GFR progress over time and what are the optimal monitoring times?**

The rate of decline (mL/min/1.73 m^2^/year) in reference GFR, and the difference between reference GFR and estimated GFRs (referred to as error), measured every 12 months will be modelled over time using a longitudinal linear or nonlinear (exponential decline) random coefficients regression model to estimate average and variability in disease progression and error. Parameters of the model for each outcome will be estimated using maximum likelihood. Covariates to be explored in the model will be as described above. The effect of covariates on the population average intercept and longitudinal time effect parameters will be assessed. The method of backward elimination will be used to remove covariates which are not significant from the model. A linear relationship between disease progression and drug name or drug class will be explored. Analysis will be undertaken using NONMEM version 7.1.2, R open source software and PFIM version 3.2.2 optimal design algorithms (R open source software). The PFIM algorithms will be used to calculate the D-optimal [62] sampling times from the disease progression model based on reference GFR for individuals with diabetes and/or proteinuria, and for those individuals with neither of these conditions. Optimal monitoring strategies will be selected from a set of designs and for important subgroups of the population found to be significant in the disease progression model. The monitoring strategies identified will be used as the basis for further simulations.

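### Baseline GFR is a covariate on the slope of a model whose first outcome value is, on the natural reading, the same measurement, so shared error biases towards faster decline at higher GFR

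*Protocol article*

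**What the plan says.** In the Protocol article, Sample size calculations, item 2, the sub-study size is justified by the covariates to be studied: "A sample size of 375 was chosen based on practical considerations to allow investigation of twelve covariates of interest". The list includes "duration of diabetes, ethnicity, albuminuria, baseline GFR, blood pressure, body mass index".

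Under Data analysis, Sub-study of patterns of disease progression, the outcomes are reference GFR and the difference between reference and estimated GFR, "measured every 12 months will be modelled over time using a longitudinal linear or nonlinear (exponential decline) random coefficients regression model". The list is carried into that model: "Covariates to be explored in the model will be as described above". Each covariate may act on two parameters: "The effect of covariates on the population average intercept and longitudinal time effect parameters will be assessed". Selection is by significance: "The method of backward elimination will be used to remove covariates which are not significant from the model".

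The abstract places reference GFR at baseline and 3 years for the whole cohort, and for the sub-study adds: "Additional reference GFR measurements will be undertaken after 1 and 2 years to enable a model of disease progression and error to be built". The modelled times are therefore 0, 1, 2 and 3 years, and the baseline iohexol result is the time-0 outcome. On the size of the error, Sample size calculations, item 3, says "The biological variation of GFR has been estimated at approximately 10" per cent. The Measuring GFR section gives a reported range of 5.5% to 11.6%.

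**The concern.** A participant whose baseline iohexol result is high by chance has a high covariate value. The same chance error lifts the first point of the series, so the fitted line falls more steeply. This is regression to the mean, and it always pushes the baseline-by-time coefficient in the negative direction. On the intercept, the covariate largely predicts itself.

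Backward elimination cannot tell this artefact from a real association. The sub-study analysis section then chooses monitoring strategies for subgroups that prove significant in the model, and the Modelling monitoring strategies section takes determinants of progression from this sub-study as an input. The model may also take an exponential form, in which higher GFR really does fall faster in absolute terms, so the artefact would resemble a pattern the analysis is looking for.

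**Working it through.** The sub-study has no power figure to reproduce. Its size is 3 × 125 = 375, which agrees, and it was set on practical grounds.

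**Inputs from the documents:** times 0, 1, 2, 3 years; n = 375; within-person CV of 10% (planning) and 5.5% to 11.6% (reported range).

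**Assumptions, not in the documents:** mean measured GFR 45; between-person SD s_b of 8.4 (uniform over the 30–59 entry range, 29/√12), 12 or 15; SD of true slopes s_s of 2 or 4 mL/min/1.73 m²/year; no true link between starting GFR and slope; two-sided 5% retention; no dropout.

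**Step 1, weight of the baseline value.** The mean time is 1.5 and the sum of squared deviations is 2.25 + 0.25 + 0.25 + 2.25 = 5. The least-squares slope gives the baseline value a weight of −1.5/5 = −0.3.

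**Step 2, expected coefficient.** b = −0.3 × s_e² / (s_b² + s_e²). At a CV of 10%, s_e = 4.5 and s_e² = 20.25.
- s_b 8.4: −0.3 × 20.25/90.81 = −0.067
- s_b 15: −0.3 × 20.25/245.25 = −0.025

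At a CV of 5.5%, s_e² = 2.475² = 6.13.
- s_b 8.4: −0.3 × 6.13/76.69 = −0.024
- s_b 15: −0.3 × 6.13/231.13 = −0.008

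**Step 3, chance of significance.** SE² = [s_s² + s_e²/5 − b²(s_b² + s_e²)] / [375(s_b² + s_e²)], and the chance is Φ(|b|/SE − 1.96) + Φ(−|b|/SE − 1.96). For a CV of 10%, s_b 8.4 and s_s 2, the numerator is 4 + 4.05 − 0.41 = 7.64 and the denominator 375 × 90.81 = 34,054. This gives SE = 0.0150, |b|/SE = 4.47 and a chance of 99%.

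| CV | s_b | Spurious extra decline per 10 mL/min (mL/min/1.73 m²/year) | Chance, s_s 2 | Chance, s_s 4 |
|---|---|---|---|---|
| 5.5% | 8.4 | 0.24 | 43% | 17% |
| 5.5% | 12 | 0.12 | 25% | 11% |
| 5.5% | 15 | 0.08 | 18% | 9% |
| 10% | 8.4 | 0.67 | 99% | 80% |
| 10% | 12 | 0.37 | 91% | 54% |
| 10% | 15 | 0.25 | 76% | 39% |
| 11.6% | 8.4 | 0.84 | >99% | 94% |
| 11.6% | 12 | 0.48 | 98% | 75% |
| 11.6% | 15 | 0.32 | 91% | 58% |

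**Step 4, does the random coefficients model remove it?** No. Forty maximum likelihood fits (CV 10%, s_b 8.4, s_s 2), with baseline on both intercept and slope, gave a mean coefficient of −0.065, significant in 39 of 40. The observed baseline enters as a fixed covariate, so random effects do not correct its error.

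**Step 5, which spread is plausible?** Entry is on eGFR, not measured GFR. The P30 values of 81% and 86% in the sample size section imply, for unbiased normal relative error, a scatter of 30/1.31 = 22.9% and 30/1.48 = 20.3%. At GFR 45 that is 10.3 and 9.1 mL/min. Added to an eGFR variance of about 70, the observed baseline variance is about 176 or 154. Then b = −0.3 × 20.25/176 = −0.035, or −0.3 × 20.25/154 = −0.039. This is close to the s_b 12 row.

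**Step 6, do the alternatives work?** Under the same no-relation assumption:
- No baseline covariate, with intercept–slope covariance estimated: implied slope-on-intercept coefficient 0.003 (SD 0.020 over 40 fits).
- Baseline kept as covariate, time 0 dropped from the outcome: coefficient about 0.000 to 0.001, significant in 5–6% of runs.
- Baseline GFR with error independent of the iohexol value: coefficient about 0, significant in 5–6% of runs.

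**The case against.** The strongest objection is that the article never says the covariate is the measured value. Elsewhere it writes eGFR for estimates and reference or iohexol GFR for measurements, and baseline GFR matches neither exactly. Sub-study visits also yield eGFRs. If an eGFR is meant, the artefact on the reference-GFR slope largely vanishes. This stands as a limit on confidence. It does not dispose of the point: the modelled outcome is reference GFR, and the prognostic model in the main study says eGFR when it means estimates, so measured is the likelier reading. Under the other reading, the second outcome (reference minus estimated GFR) shares error with the covariate instead.

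A second objection is that coding and covariance structure belong in an analysis plan, and that nothing in the article excludes correlated random effects. That is fair for the covariance structure. But the article itself names the covariate, the parameters it may act on and the selection rule, and the objection is to that combination.

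A third objection concerns size. With a narrow GFR range of 30–60 (variance 75) and a CV of 10%, b = −0.3 × 20.25/95.25 = −0.064, or 1.3 mL/min/1.73 m²/year between GFR 35 and 55. A reader might take this as the expected effect and infer that backward elimination is bound to keep it. The documents do not support that. With the wider spread of Step 5, the same contrast is about 0.7 to 0.8. Retention depends on unstated spreads, and slopes may vary widely in a sub-study that is about half diabetic and/or proteinuric.

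A reader might also infer that the D-optimal sampling times and the cost-effectiveness results are thereby wrong. The article computes those times by diabetes and/or proteinuria status, not by baseline GFR. Baseline GFR could enter only as a subgroup found significant, and no change in a sampling time, monitoring strategy or cost result has been shown.

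**Conclusion.** The concern holds, with moderate confidence because the covariate is not labelled. If the time-0 iohexol value is meant, the direction of bias is certain. At the protocol's planning CV, the spurious effect is 0.25 to 0.67 mL/min/1.73 m²/year per 10 mL/min of baseline, for a between-person SD of 15 down to 8.4. The chance of reaching 5% significance is then about 39% to 99%. At a CV of 5.5%, the effect is 0.08 to 0.24 and the chance 9% to 43%.

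For scale, the Background cites ageing-related decline of about 1, and mean declines of 1.1 to 3.6, mL/min/1.73 m²/year in older adults with stage 3 CKD. The artefact is therefore material at 10% and minor at 5.5% with a wide spread. The mean GFR, the spreads, the retention level and complete follow-up are assumptions. What is at stake is a false determinant of progression that could define a monitoring subgroup or pass into the monitoring model. Actual damage to those outputs is possible but not demonstrated.

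**What to change.** State which baseline GFR is meant. Do not use the time-0 iohexol GFR as a fixed covariate in the reference-GFR model. Let the random intercept and slope be correlated, estimate their covariance, and report the implied slope-on-intercept relation as the dependence of decline on starting GFR.

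If a baseline covariate is wanted, there are two options. One is to drop the time-0 value from the outcome. The other is to use a baseline GFR whose error is independent of the iohexol value. An eGFR would serve for the reference-GFR outcome, but not for the reference-minus-estimated outcome, which contains the eGFR's own error.

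The change needs no extra participants, visits or assays. The cost is slightly less direct reporting of the baseline effect, or one fewer outcome time point if time 0 is dropped.
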